**Fig. 2 Fig2:**
[figure not shown]
Example of magnetic resonance imaging (MRI) image acquisition. Left: cervical, thoracic and lumbar scout views stitched together with three osteolytic lesions identified at T5, T11 and L2. Top, middle: lumbar scout view at higher resolution with the L2 vertebra outlined. Bottom, middle: example data outputs provided by regional analysis. Right: slice by slice, cephalad to caudal, transverse view at each level of the L2 lesion, with an example colour map and tumoural analysis of one slice in isolation

##### Biomarkers

Metastatic tumour biomarkers, hypoxia-inducible factor 1-alpha (HIF-1α) and transformation growth-like factor beta (TGF-β) will be serologically examined to measure tumoural hypoxic activity and growth activity respectively; identified as synergistic drivers of metastatic tumour progression [45, 80–84]. Fasted serological and first-void samples for urianalysis will also be collected within 48 h of baseline and post-intervention testing sessions to measure bone metabolic activity and systemic inflammation. Specifically, bone formation marker, amino-terminal propeptide of type 1 procollagen (P1NP); bone resorption marker, amino-terminal collagen type-I telopeptide (NTx); bone disorder marker, alkaline phosphatase (ALP), inflammation marker, C-reactive protein (CRP) and fasting glucose and lipid profiles will be examined. All fasted serological and first-void biomarkers will be collected in the morning, and assessed by the same accredited laboratory (Australian Clinical Laboratories, Perth, Western Australia).

##### Anthropometry

Stature will be recorded to the nearest 0.1 cm using a wall-mounted stadiometer (Model 222, Seca, Hamburg, Germany), with body mass recorded to the nearest 0.1 kg using an electronic scale (AE Adams CPW Plus-200, Adam Equipment Inc., CT, USA), with body mass index (BMI) calculated as weight divided by height in metres squared (kg/m^2^). Waist and hip circumferences are defined as the mid-point between the 10th rib and the iliac crest and the level of the greater trochanter, respectively, with the waist-to-hip ratio calculated. Femoral length will be measured from the greater trochanter to the knee-joint axis and tibial length will be measured from the knee-joint axis to the medial malleolus. Waist circumference, hip circumference, femoral length and tibial length will be measured to the nearest 0.1 cm using a constant-tension, retractable measuring tape (Model 4414, Tech-Med Services, NY, USA). Stature, waist circumference and hip circumference will be measured in triplicate in each participant, with the average of each variable retained for analysis.

##### Musculoskeletal health

Whole-body, segmental (axial and appendicular) and regional (spinal and total hip) scans will be performed to examine bone area (BA), areal bone mineral content (aBMC), areal bone mineral density (aBMD) and lean mass using dual-energy x-ray absorptiometry (DXA; Hologic Discovery A, Waltham, MA, USA). Whole-body and appendicular segmentations will be analysed in accordance with [name] and colleagues [85]. Regional analyses (lumbar spine, total hip, femoral neck, trochanter, Wards triangle) will be performed in accordance with Hologic’s manufacturer specifications [86].

Appendicular, non-lesion control sites will be scanned to quantify bone material, structure and strength using peripheral quantitative computed tomography (pQCT; XCT-3000, Stratec, Pzochienheim, Germany). Specifically, trabecular, cortical, marrow and total volumetric density (Tb.vBMD, Ct.vBMD, Ma.vBMD, Tt.vBMD); trabecular, cortical, marrow and total cross-sectional area (Tb.Ar, Ct.Ar, Ma.Ar, Tt.Ar); cortical thickness (Ct.Th); stress-strain index (SSIPOL); absolute fracture load (FL.Ab) and relative fracture load (FL.Rel) of the left femur (4% and 33% slices) and left tibia (4%, 14%, 38% and 66% slices) will be measured and analysed in accordance with [name] and colleagues [87, 88]. Muscle cross-sectional area (Mu.Ar) will also be quantified.

##### Adiposity

Whole-body, segmental and central subcutaneous adipose tissue (fat mass), central visceral adipose tissue (VAT; area, mass and volume) and android-to-gynoid ratio will be measured using DXA. Whole-body and appendicular segmentations will be generated in accordance with [name] and Colleagues [85]. Fat area (Fa.Ar) and muscle density (Mu.Den) of the thigh and shank will be measured using pQCT [87, 88], as an indication of subcutaneous and intramuscular fat infiltration, respectively.

##### Objective measures of physical function

Muscle strength, aerobic capacity and physical function will be assessed. Muscle strength will be measured using the one repetition maximum (1RM) test for the leg extension exercise. This exercise was chosen as it can be safely performed by all patients included in this study. The 400 m walk test and Timed Up and Go test will be used as measures for aerobic capacity and physical function, respectively. In addition, patients will also undergo a comprehensive balance test (NeuroCom Smart Balance, Natus Medical Inc., USA).

##### Quality of life, anxiety, distress, insomnia and physical activity

Health-related quality of life outcomes for general health, pain, vitality, social functioning, emotional role and mental health will be measured using the Short Form 36 (SF-36, IQOLA) survey. In addition, the European Organisation for Research and Treatment of Cancer (EORTC) Quality of Life Questionnaire, Module 3 (QLQ-30) (cancer) and EORTC Breast Cancer, Module 23 (BR-23) surveys will also be provided to measure cancer-specific indices of quality of life. The FACIT Bone Pain (FACIT-BP) questionnaire will be used to examine bone pain, and the Brief Symptom Inventory (BSI-18) will be used to assess psychological distress for the anxiety, depression, somatisation and global distress severity domains. The Insomnia Severity Index (ISI) will be used to measure sleep quality disturbance, and the Godin Leisure-Time Exercise questionnaire will be applied to examine self-reported physical activity levels.

### Exercise programme

Participants assigned to the exercise arm will be required to participate in a modular, multi-modal exercise programme (M3EP), which includes spinal isometric training (SIT) for 12 weeks. The combined M3EP-SIT programme requires participants to attend three clinic-based exercise sessions each week spanning 60 min in duration (including warm up and cool down), supervised by an accredited exercise physiologist (AEP; Exercise and Sport Science Australia). Participants will also be asked to perform the SIT portion of the programme during two additional home-based exercise sessions each week spanning 15 min in duration. During combined M3EP-SIT sessions, spinal isometric training will be provided first, followed by the modular multi-modal exercise programme (Table 3).

**Table 3 Tab3:** Weekly distribution of testing, M3EP and SIT exercise sessions across the exercise intervention

	Monday	Tuesday	Wednesday	Thursday	Friday	Saturday	Sunday
Week 0	Baseline testing						
Week 1 to Week 2	SIT	–	SIT	–	SIT	REST	REST
	M3EP		M3EP		M3EP		
Week 3 to Week 12	SIT	SIT	SIT	SIT	SIT	REST	REST
	M3EP		M3EP		M3EP		
Week 13	Post-Intervention Testing						

Clinic exercise sessions occur on Monday, Wednesday and Friday; home isometric exercise sessions occur on Tuesday and Thursday. Spinal isometric exercises are provided at the start of all clinic exercise sessions (following a general warm up). Home-based SIT starts from week 3 onwards to enable appropriate familiarisation and training during the first 2 weeks of the programme

*Abbreviations*: *SIT* spinal isometric training (15 min), *M3EP* modular multi-modal exercise programme (60 min)

The M3EP component of the programme will comprise resistance, aerobic and flexibility exercises in accordance with [name] and colleagues [48, 51, 55–58]. This M3EP component is designed to minimise loads on affected skeletal sites throughout the body. Exercise prescriptions for all activities will be modified based on the location and extent of bone metastases (Table 4). Resistance exercise will be set using repetition maximums (RM). Participants will be asked to perform six different resistance exercises using major muscle groups, subject to the location and extent of bone metastases, at 10–12 RM for three sets per exercise to achieve moderate intensity and volume. Aerobic exercise will be set using age-predicted heart rate maximum (HRmax). Participants will engage in cardiovascular exercise using various modes including treadmill, cycling and rowing ergometers, performed at 60–85% HRmax for 20–30 min using heart rate monitors (Polar Electro Oy, Finland). Flexibility exercise will involve static stretching of muscles at all joints considered important for function, and for all muscles engaged during the session. All stretches will involve 2–4 sets per muscle group with a 30–60 s hold per set.

**Table 4 Tab4:** Modular multi-modal exercise programme for patients with bone metastases [48, 51, 56, 57]

Metastasis site	Resistance			Aerobic		Flexibility
	Upper	Trunk	Lower	WB	NWB	Static
Pelvis	√	√	√**		√	√
Lumbar spine	√		√		√	√***
Thoracic spine/ribs	√*		√	√	√	√***
Proximal femur	√	√	√**		√	√
All regions	√*		√**		√	√***

*Abbreviations*: *WB* weight bearing (e.g. walking), *NWB* non-weight bearing (e.g. cycling)

√ represents target exercise region

*Exclusion of shoulder flexion/extension/abduction/adduction - inclusion of elbow flexion/extension

**Exclusion of hip extension/flexion - inclusion of knee extension/flexion

***Exclusion of spine/flexion/extension/rotation

The SIT component of the programme will comprise exercises that isometrically load deep spinal muscles as well as the larger superficial trunk musculature. These will be performed five times per week. Three sessions will be supervised by an AEP with the M3EP component at an exercise clinic, with an additional two sessions self-managed by the participant. This SIT component is designed to directly target and stimulate spinal lesion site(s) through muscular contraction, thus isometric exercises have been designed to activate the full spinal column due to the commonality of lesions in cervical, thoracic and lumbar regions, the feasibility of which has been demonstrated [59]. The SIT programme will require the participants to perform five exercises in whole and partial weight-supported prone and supine positions on the floor, whilst maintaining a neutral spine position (isometrically) during gentle and dynamic accessory movements. If floor exercises are contraindicated for the patient due to physical restrictions, alternate seated and standing isometric exercises will be provided. All patients will be initially provided with familiarisation of breathing technique, trunk stabilisation and hip control. Basic spinal isometric exercises will first be used to ensure safe and correct technique prior to progressing to intermediate or more challenging exercises, which include less stability or dynamic accessory movements [89]. Isometric progression of patients from beginner to advanced exercises will be individually determined on the basis of their physical capabilities and known contraindications. An assortment of spinal isometric exercises canvassing beginner to advanced and floor to standing are described in Additional files 1 and 2, respectively, with photographic demonstration of prone and supine exercises in Additional file 3.

### Statistical analysis

Data will be analysed using SPSS (IBM Corporation; Chicago, IL, USA). Normality of distribution of continuous variables will be determined by Shapiro-Wilk test and visual inspection of the data. Analyses will include standard descriptive characteristics, the *t* test and two-way (group × time) repeated measures analysis of variance (ANOVA) (or analysis of covariance as appropriate) to examine differences between groups over time. Any data that are not normally distributed will be log-transformed or non-parametric tests will be used. The Pearson chi-square test will be used to analyse categorical variables. An alpha level of *p* ≤ 0.05 will be applied to establish statistical significance. Effect sizes will also be calculated in accordance with Hopkins [90]: *d* ≥ 0.2 is small; *d* ≥ 0.6 is moderate; *d* ≥ 1.2 is large; *d* ≥ 2.0 is very large. Incomplete data and missing values will be primarily managed using an intention-to-treat approach [91] with multiple imputation, specifically using maximum likelihood imputation of missing values. To ensure the robustness of our findings, a secondary sensitivity analysis [92, 93] will be conducted using a complete-cases approach.

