### Randomisation

Patients will be randomly allocated in a ratio of 1:1 to the two study arms: exercise or usual care, stratified by age (≤ 60 years, > 60 years), hormone receptor (HR) status (HR+, HR-) [69] and time since completion of palliative radiotherapy to target spinal lesions (< 3 months, ≥ 3 months) and/or time since commencing or changing hormone therapy and/or chemotherapy (< 3 months, ≥ 3 months). A research officer with no patient contact will be responsible for randomisation of patients into either group using a computer-generated code through a random-assignment programme. Study investigators and exercise physiologists conducting testing procedures will be blinded to group allocation. Only exercise physiologists outside the research team will be permitted to deliver the exercise intervention to participants in order to maintain integrity of the blinding process.

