### Participants

A total of 40 women (20 subjects per arm) with breast cancer and stable osteolytic bone metastases in cervical, thoracic and/or lumbar vertebrae will be invited to participate. They will be included if they have not engaged in regular exercise in the past 3 months (defined as undertaking structured aerobic and/or resistance training two or more times per week). Due to the novelty of this explorative clinical trial, our sample size is based on previous preclinical animal studies [13, 70–72], human pilot studies [14, 56, 58, 73, 74] and consideration of the ability to recruit patients with advanced breast cancer and osteolytic bone metastases during the trial. Specifically, to achieve 80% power at an alpha level of 0.05 (two-tailed), 16 subjects per group are required to demonstrate a meaningful difference (effect size ≥ 1.0) at the completion of the study for the primary endpoint, and most secondary endpoints. To account for an attrition rate of up to 25%, 40 subjects will be randomised equally between the study arms (exercise, *n* = 20; control, *n* = 20).

Patients are permitted to receive radiotherapy for non-spinal bone metastases while enrolled in this trial. Patients require medical clearance prior to enrolment, therefore must achieve an Eastern Cooperative Oncology Group (ECOG) performance status ≤ 1, and must not have any acute illness, significant bone pain or cardiovascular or neurological disorders that could inhibit exercise participation as judged by their managing physician. All participants must provide written informed consent prior to participation. Patients will be excluded from this trial if they are receiving experimental treatments. The protocol has been approved by the Human Research Ethics Committee (HREC) of Edith Cowan University (ECU), Project ID 14266 [name]; St John of God Hospitals (SJOG), Project ID 969 and Sir Charles Gairdner and Osborne Park Health Group (SCGOPHG), Project ID 2016–118. This trial is also registered with the Australia and New Zealand Clinical Trails Register (ANZCTR), Trial ID ACTRN-1261600136842.

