### Measurements

Primary and secondary endpoints will be measured at baseline (week 0), post-intervention (week 13) and through-out the 12-week on-trial period (Table 1).

**Table 1 Tab1:** Assessments of study feasibility

Measures	Time of collection
Recruitment and completion	
- Referred patients	Trial completion
- Eligible patients	Trial completion
- Enrolled patients	Trial completion
- Eligibility rate	Trial completion
- Recruitment rate	Trial completion
- Trial completions	Trial completion
- Patient withdrawals	Trial completion
- Patient drop-outs	Trial completion
- Trial contamination	Trial completion
Patient safety (control arm)	
- Number of adverse events	Tri-weekly record
- Severity of adverse events	Tri-weekly record
- Number of skeletal complications	Tri-weekly record
Patient safety (intervention arm)	
- Number of adverse events	At each exercise session
- Severity of adverse events	At each exercise session
- Number of skeletal complications	At each exercise session
Program tolerance (intervention arm)	
- Pre-sessional bone pain	At each exercise session
- Pre-sessional fatigue	At each exercise session
- Sessional rating of perceived exertion	At each exercise session
- Sessional tolerance	At each exercise session
Program adherence (intervention arm)	
- Number of completed sessions	Post intervention
- Number of missed sessions	Post intervention
Program compliance (intervention arm)	
- Prescribed vs. actual exercise completed (for each exercise mode).	Post intervention
- Percent of total volume completed (for each exercise mode).	Post intervention

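### For continuous secondary outcomes measured once before and once after treatment, the lead analysis (group × time ANOVA) is less precise than baseline-adjusted ANCOVA, which should be fixed as the main model

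*Protocol article*

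**What the plan says.** The Statistical analysis section names descriptive statistics, the t test and a two-way group × time "repeated measures analysis of variance (ANOVA) (or analysis of covariance as appropriate) to examine differences between groups over time". It names no covariates and gives no rule for choosing between the models. Data that are not normally distributed are to be log-transformed or tested non-parametrically.

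On timing, the Measurements section states "Primary and secondary endpoints will be measured at baseline (week 0), post-intervention (week 13"), and Table 2 shows one baseline and one post-intervention assessment for the imaging, biomarker, body-composition, function and questionnaire outcomes.

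The Randomisation section states "Patients will be randomly allocated in a ratio of 1:1 to the two study arms: exercise or usual care, stratified by age", and goes on to hormone-receptor status and treatment timing. The timing part joins time since radiotherapy and time since starting or changing systemic therapy by an and/or.

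The sample size in the Participants section reads "to achieve 80% power at an alpha level of 0.05 (two-tailed), 16 subjects per group are required" to show a "meaningful difference (effect size ≥ 1.0) at the completion of the study for the primary endpoint, and most secondary endpoints". It continues: "To account for an attrition rate of up to 25%, 40 subjects will be randomised equally between the study arms".

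**The concern.** When each patient has one baseline and one follow-up value, the group × time interaction is the difference between arms in mean change. Subtracting the whole baseline value is optimal only if the regression of follow-up on baseline has slope 1. Otherwise the change score carries baseline noise into the comparison, and it over-corrects when the arms differ at baseline by chance, which is quite possible with 15 to 20 patients per arm. ANCOVA estimates the slope from the data and avoids both problems.

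At stake is the precision of the preliminary-efficacy estimates (tumour volume, biomarkers, body composition, function) that the article intends as a foundation for phase II and III trials. Because the alternative to ANOVA is left to judgement, the same endpoint could also be analysed in more than one way.

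**Working it through.** **The plan's own figure.** Inputs from the Participants section: two-sided alpha 0.05, power 80%, standardised difference 1.0. The normal approximation gives n = 2 × (1.960 + 0.842)² / 1.0² = 15.7, so 16 per group, as stated. The exact t test has 78.1% power at 16 and needs 17. With 20 randomised per arm and 25% attrition, 20 × 0.75 = 15 complete, and 15 per arm is used below.

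**Equivalence of the two tests.** On a simulated data set with 16 per arm and two time points, the interaction F statistic was 13.559, equal to the square of the change-score t statistic.

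**Variances.** Take the same SD σ at both times and correlation ρ. The variance factor per patient, in units of σ², is:
- week-13 value alone: 1
- change score: 2(1 − ρ)
- ANCOVA on baseline: 1 − ρ²

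The ratio of ANCOVA to change is (1 − ρ²) / [2(1 − ρ)] = (1 + ρ)/2, which is below 1 for every ρ < 1.

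**Power.** With d = 1.0 in week-13 SD units, n = 15 per arm and variance factor v, the noncentrality is d / √(2v/n). At ρ = 0.3 this is 1/√(2 × 1.40/15) = 2.315 for change and 1/√(2 × 0.91/15) = 2.871 for ANCOVA. Power from the noncentral t with 28 degrees of freedom is shown below. The last column charges ANCOVA for estimating the slope and for chance baseline imbalance (27 degrees of freedom, variance × (1 + 1/26)).

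| ρ (assumed) | v, change | v, ANCOVA | ratio | power, change | power, ANCOVA | ANCOVA, costs charged |
|---|---|---|---|---|---|---|
| 0.3 | 1.40 | 0.91 | 0.65 | 60.8% | 79.1% | 77.5% |
| 0.5 | 1.00 | 0.75 | 0.75 | 75.3% | 86.3% | 84.9% |
| 0.7 | 0.60 | 0.51 | 0.85 | 92.7% | 95.9% | 95.2% |

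The week-13 comparison alone has 75.3% power at 15 per arm. Since 2(1 − ρ) > 1 when ρ < 0.5, the change-score test is weaker than that simple comparison below ρ = 0.5.

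**Sensitivity to n.** At 16 per arm, with costs charged, the pairs are 64% and 80% (ρ = 0.3), 78% and 87% (0.5), 94% and 96% (0.7). At 20 per arm and ρ = 0.5 they are 87% and 94%.

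**Cost of more covariates.** Reducing 28 degrees of freedom to 24 (baseline plus three strata terms) moves ANCOVA power at 15 per arm from 79.1% to 78.7%, from 86.3% to 85.8% and from 95.9% to 95.7%.

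**Value of the strata.** In a simulation (16 per arm, three binary strata as main effects, 5,000 runs per setting, ρ = 0.5), adding the strata to baseline-adjusted ANCOVA changed power as follows:
- strata explain none of the residual variance: 87.1% to 86.0%
- strata explain 10%: 88.8% to 89.8%
- strata explain 20%: 89.2% to 92.6%

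With non-prognostic strata the loss was 1.6 points at ρ = 0.3 and 1.0 point at ρ = 0.7.

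**The case against.** The strongest reply is that the plan does not commit to the weaker model: ANCOVA is named as an alternative, and a fuller analysis plan may settle the choice and list covariates. That stands in part. The point is not that ANCOVA is absent, but that the published text puts the change-score analysis first and ANCOVA second, with no rule for choosing.

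The size of the loss is also open to challenge. It depends on a correlation that the article does not give, and 15 per arm is the worst case of the stated attrition. At ρ = 0.7 the gain is about three points, and at ρ = 0.8 both methods reach about 99%. The article does not say which SD the effect size refers to. If it is the SD of change, the change-score test has the power that was planned. These objections stand and limit the point.

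Three stronger readings are tempting, and the text does not support them:
- A reader might infer that the analysis ignores the randomisation strata. The article is silent on covariates, which a condensed text may leave to the full plan. Nor can a gain from adjusting for them be taken for granted, as the simulation shows.
- A reader might infer that normality testing decides between t test, ANOVA and ANCOVA. The section ties only log transformation and non-parametric tests to non-normality, judged by Shapiro-Wilk and by visual inspection.
- A reader might infer that the trial's primary conclusion is at risk. The primary endpoint is feasibility and safety, with tolerance, adherence and compliance recorded in the exercise arm only. This model does not bear on it.

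**Conclusion.** The point holds for the continuous secondary outcomes with one baseline and one week-13 value. The lead method is a change-score test in another form. Under equal variances its treatment-effect variance exceeds that of baseline-adjusted ANCOVA for any ρ < 1, apart from the small cost of estimating one slope. ANCOVA variance is 35%, 25% and 15% smaller at ρ = 0.3, 0.5 and 0.7. In power at 15 completers per arm, the gain is about 18, 11 and 3 points before the small covariate costs.

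These figures assume equal SDs at both times, an effect size in week-13 SD units and the chosen values of ρ. It would go too far to say that the sample size is contradicted: the wording suggests an end-of-study comparison but does not define the SD. This is a low-cost improvement that the sponsor should make. It is not a flaw in the primary analysis.

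**What to change.** In the Statistical analysis section, make ANCOVA of the week-13 value on arm and baseline value the main model for every continuous secondary outcome, and report the adjusted difference with its 95% confidence interval. Add the stratification factors as main effects only: age group, hormone-receptor status and the treatment-timing factor. First resolve the and/or wording of the timing factor to the variable actually used in randomisation, since the term cannot be coded until then.

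Set the log scale in advance for skewed markers and for tumour volume. Keep the group × time ANOVA and the non-parametric tests as supportive analyses.

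The change is one of wording. Baseline values and stratification factors are already collected. Four degrees of freedom are spent, worth less than one point of power. If the strata turn out not to be prognostic, the net cost of including them is about one point (1.0 to 1.6 in the simulation).

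### The primary missing-data method is named in two ways that do not match; one reading, a single maximum likelihood fill-in, would at least double the type I error of the secondary tests at 25% attrition

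*Protocol article*

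**What the plan says.** All references are to the protocol article.

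- **Primary handling of missing data** (Statistical analysis): an intention-to-treat approach "with multiple imputation, specifically using maximum likelihood imputation of missing values".
- **Sensitivity analysis** (Statistical analysis): "To ensure the robustness of our findings, a secondary sensitivity analysis [92, 93] will be conducted using a complete-cases approach". No other sensitivity analysis is named.
- **Tests** (Statistical analysis): a t test and "two-way (group × time) repeated measures analysis of variance (ANOVA) (or analysis of covariance as appropriate"), judged at p ≤ 0.05.
- **Size and attrition** (Participants): "to achieve 80% power at an alpha level of 0.05 (two-tailed), 16 subjects per group are required" for a standardised effect of 1.0 or more, and then "To account for an attrition rate of up to 25%, 40 subjects will be randomised equally between the study arms", which gives 20 per arm.
- **Visits** (Measurements and Table 2): the pre/post outcomes are measured at week 0 and week 13.
- **Primary endpoint** (Primary Endpoint, Feasibility): recruitment, completion, safety, tolerance, adherence and compliance. Tumour morphology, biomarkers, body composition, function and questionnaires are secondary.

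**The concern.** Multiple imputation creates several completed datasets, analyses each and pools the results, so that uncertainty about the missing values enters the standard error. A maximum likelihood fill-in replaces each gap with a model-based value. If that is done once and the result goes into a t test, ANOVA or ANCOVA, the software treats 40 patients as observed when perhaps 30 were. The word 'specifically' presents the second procedure as the definition of the first, so two competent analysts could follow the sentence and report different p-values.

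What is at stake is the preliminary efficacy signal. The article says the results will be the basis for phase II and III trials. An anti-conservative test could produce a false tumour or biomarker signal, and an imputation model without arm could dilute a true one.

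There is a second, smaller point. Complete cases is offered as the guarantee of robustness, but it does not address drop-out that depends on the unseen week-13 value. That mechanism is plausible in a palliative population in which the article itself describes progression, bone pain and fracture.

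**Working it through.** **The plan's own figure.** The plan states no error rate for its missing-data method, so the only figure to reproduce is the sample size. The normal approximation for d = 1.0, two-sided 0.05 and 80% power gives 16 per group, as stated (the exact t test gives 17). Then 16 × 1.25 = 20 per arm, or 40 in total. With 25% lost, 20 × 0.75 = 15 per arm are observed.

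**Inputs.**
- From the document: 20 per arm, alpha 0.05, attrition up to 25%, two visits, group × time ANOVA or ANCOVA. With two visits, the group × time test is a t test on change.
- Assumed: bivariate normal data, week-13 values missing completely at random, baseline/post correlation 0.3 to 0.9, and missing fractions of 10% and 20% besides the plan's 25%.

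**Closed-form check for ANCOVA.** Suppose the gaps are filled with fitted values from a regression of week 13 on arm and baseline, and the same model is then fitted to the filled data. The filled points lie exactly on the fitted surface, so the arm estimate and the residual sum of squares equal those from complete cases. Only the residual degrees of freedom and the apparent sample size grow. The t statistic is therefore inflated by about

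√[(37 / (n − 3)) × (40 / n)], where n is the number observed and 37 = 40 − 3.

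The test uses the critical value t(37) = 2.026. The true error is the two-sided tail of t(n − 3) beyond 2.026 divided by that factor.

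| Missing | n observed | Factor | 2.026 / factor | True error |
|---|---|---|---|---|
| 25% | 30 | √(37/27 × 40/30) = 1.352 | 1.499 on 27 df | 0.145 |
| 20% | 32 | √(37/29 × 40/32) = 1.263 | 1.604 on 29 df | 0.119 |
| 10% | 36 | √(37/33 × 40/36) = 1.116 | 1.815 on 33 df | 0.079 |

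**Simulation under no effect** (20 per arm, 3,000 to 8,000 runs per setting). Rejection rate at nominal 0.05:

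| Reading of the sentence | 25% missing | Lower missingness |
|---|---|---|
| One ML fill-in, arm in model, group × time | 0.11-0.14 | 0.09-0.12 at 20% |
| One ML fill-in, arm in model, ANCOVA | 0.14-0.155 | about 0.12 at 20% |
| One ML fill-in, arm in model, either test | see above | 0.06-0.09 at 10% |
| One random draw per gap, arm in model | 0.10-0.13 | – |
| One ML fill-in, arm not in model | 0.044-0.057 | 0.054 at 20% |
| Several draws at fixed ML estimates, pooled (ANCOVA, correlation 0.5) | 0.071 | 0.064 at 20% |
| Proper multiple imputation, Rubin's rules (10 imputations, small-sample df) | 0.042-0.051 | 0.057 at 20% |
| Complete cases | 0.043-0.055 | 0.054 at 20% |

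The closed form and the simulation agree.

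**Dilution when arm is left out.** A quarter of the week-13 values are then filled without any arm difference, so the expected effect is about 0.75 of the truth. With a true effect of 1.0, the simulated estimate was 0.76.

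**Informative drop-out.** In one run the true effect was zero, and exercise-arm patients with lower week-13 values were more likely to be missing (25% missing per arm, correlation 0.5). The spurious difference was 0.229 SD with complete cases and 0.228 SD with proper multiple imputation. The two agree and share the same bias.

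**The case against.** **The text never says single imputation.** This stands. The sentence can be read as multiple imputation from a likelihood-fitted model, with an error near 0.05, or about 0.07 if every draw uses fixed estimates. A reader might infer that the plan has chosen a single fill-in and that its p-values are therefore too small. The wording does not support that: it leaves incompatible readings open, and the inflation belongs to one of them.

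**Inflation also needs arm in the imputation model and attrition near the ceiling.** This stands too. The article does not specify the model, and 25% is an upper limit.

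**The primary endpoint is untouched.** Largely right. Tolerance, adherence and compliance are assessed in the exercise arm only, so no group × time test applies to them. A reader might also infer that sessions after withdrawal, or outcomes after death, would be imputed. Nothing says so: adherence is defined by completed and missed sessions, and Table 1 counts withdrawals and drop-outs in their own right.

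**Complete cases is a legitimate check.** Partly right. It would tend to expose the variance defect, since it holds about 0.05 where a single fill-in does not. Nor is its assumption always stronger: complete-case ANCOVA adjusting for baseline is valid when missingness depends only on baseline and arm. It does not probe departures from missing at random.

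**Details belong in the SAP.** True of the number of imputations, the covariate list and the degrees of freedom; their absence is no finding here. But the article does name its primary method, and an SAP would have to override one half of that sentence.

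**Conclusion.** The point holds as an ambiguity with consequences. The primary missing-data rule names two procedures as one. Carried out as one ML fill-in with arm in the model, it gives a type I error of about 0.11-0.14 for group × time and about 0.15 for ANCOVA at 25% missing, and about 0.06-0.09 at 10%. Without arm the error is held, but the effect is diluted by about a quarter. Proper multiple imputation stays near 0.05.

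These sizes rest on normal data, values missing completely at random and an assumed correlation of 0.3-0.9. The correlation makes little difference to the ANCOVA result. The documents give no rate of progression-related drop-out, so informative missingness is a plausible risk and not an established one.

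Severity is moderate: the effect falls on secondary efficacy outcomes of a pilot whose primary endpoint is feasibility.

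**What to change.** 1. Delete the clause that specifies maximum likelihood imputation. For the continuous secondary outcomes, state one of two methods: multiple imputation with arm and baseline in the imputation model, pooled by Rubin's rules; or a likelihood-based mixed model fitted to the observed data with no fill-in. The number of imputations and further covariates can sit in the SAP.
2. Keep complete cases, described as a check on the imputation step. Do not present it as assurance against informative drop-out.
3. Preferably add a simple delta-adjusted analysis that shifts the imputed week-13 values by a range of amounts and reports where the conclusion changes.

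The cost is a revised sentence or two and a few lines of analysis code. Recruitment, visits and data collection do not change.
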